#### Control set

This analysis set includes all subjects who were randomized to the control arm and received neoadjuvant CRT and did not violate the protocol in a way that might affect the evaluation of the effect of the study drugs on the primary objective.

### 11.2 Sample size considerations

No formal sample size calculation was performed for this safety, tolerability and feasibility phase 2 study.

Nevertheless, an informal power analysis using published data [1] reveals that an increase of 100% of surgical complications (=46%) can be excluded with 49 patients in the treatment arm (Power=0.90,  $\alpha=0.05$ ), compared to the published 23%).

### 11.3 Relevant protocol deviations

All protocol deviations will be listed in the study report.

### 11.4 Statistical analysis plan (SAP)

#### 11.4.1 Missing, unused and spurious data

In general, every effort shall be made by site staff to avoid the occurrence of missing data. However, in case data is not recorded, this must be clearly stated in the eCRF. The statistical analysis will also report the frequency of missing values.

Patients with missing data for a specific side effect will be excluded from the evaluation of this side effect. Missing data for secondary objectives will be imputed with values estimated by the predictive mean matching method using R-package “mice” (version 2.30), if appropriate.

[figure not shown]

#### 11.4.2 Primary endpoint analysis

Safety and tolerability will be assessed by comparing case numbers for any complication in the treatment arm (n=50) with the calculated 95% upper CI numbers of the calculated percentage of expected numbers of current standard therapy (Table 2). Case numbers in the control arm (n=30) will be used to validate expected numbers from current standard therapy (*i.e.* will be compared to the corresponding 95% CI lower and upper borders).

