After end of the study the case numbers of each complication will be compared to the corresponding calculated  $CI_{low}$  and  $CI_{up}$  numbers for both groups and further rated. If in both groups the numbers are between these borders,  $H_0$  is rejected and the treatment is considered as safe and tolerable. If the case numbers are above the  $CI_{up}$  border in the treatment group,  $H_0$  will be accepted for this complication and the treatment is considered unsafe. If case numbers for a specific complication are below the corresponding  $CI_{low}$  border in the control group, a new complication percentage with confidence intervals for the treatment group will be calculated using the real case numbers in the control group and the case numbers in the treatment group reassessed. For the complication "reoperation" an assessment after every 10 patients of the treatment group will be performed and if the observed case numbers are above the calculated  $CI_{up}$  border case numbers, the study will be terminated (Table 3).

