**Table 3. Reoperation cutoff values for study termination.**

| $n^1$ | $CI_{up}^2$ |
|-------|-------------|
| 10    | 4           |
| 20    | 5           |
| 30    | 7           |
| 40    | 8           |
| 50    | 10          |

Number of recruited patients in the treatment arm. Corresponding calculated  $CI_{up}$  number of cases for the complication "reoperation" [1]. If the respective case number exceeds the calculated  $CI_{up}$  number, the study will be terminated.

[figure not shown]

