## 6 STUDY OBJECTIVES

### 6.1 Primary objective

- Safety, tolerability and feasibility of sequential neoadjuvant ipilimumab and nivolumab in combination with standard neoadjuvant CRT, following surgical resection, assessed by the latest “Clavien-Dindo Classification of surgical complications” [26] (see section 9.1.2 ) and Common Terminology Criteria of Adverse Events (CTCAE) [27] (see section 9.4 ).

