### 7.1.6 Withdrawal and replacement of subjects

#### Criteria for withdrawal

Subjects may prematurely discontinue from the study at any time. Premature discontinuation from the study means that the subject did not undergo an end of study (EOS) examination as planned per protocol.

Subjects must be withdrawn under the following circumstances:

- at their own request
- if the Investigator feels it would not be in the best interest of the subject to continue
- if the subject violates conditions laid out in the consent form / information sheet or disregards instructions by the study personal
- in case of unacceptable toxicity
- in case of pregnancy of the subject
- if the entire study is terminated for medical or ethical reasons

In all cases, the reason why subjects are withdrawn must be recorded in detail in the eCRF and in the subject's medical records. Should the study be discontinued prematurely, all study materials (completed, partially completed and empty eCRFs) will be retained.

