#### Follow-up of patients withdrawn from the study

In case of premature discontinuation after study drug intake, the investigations scheduled for the EOS visit will be performed 28 days after study drug discontinuation. The subjects will be advised that participation in these investigations is voluntary. Furthermore, they may request that from the time point of withdrawal no more data will be recorded and that all biological samples collected in the course of the study will be destroyed.

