#### Replacement policy

Patients who discontinue the clinical trial before receiving the first cycle of treatment will be replaced. All other drop-outs will be included in the sample size.

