## 9.2 Adverse events (AEs)

### 9.2.1 Summary of known and potential risks of the study drug

The overall safety experience with nivolumab, as monotherapy or in combination with ipilimumab, is based on experience in approximately 12,300 subjects treated to date. Extensive details on the safety profile of nivolumab and ipilimumab, including results from other clinical studies, are available in section 5.6 of the nivolumab IB or ipilimumab IB and will not be repeated herein.

Overall, the safety profile of nivolumab in combination with ipilimumab or radiotherapy is manageable and generally consistent across completed and ongoing clinical trials. Most AEs were low-grade (Grade 1 to 2) with relatively few related high-grade (Grade 3 to 4) AEs. There was no pattern in the incidence, severity, or causality of AEs with respect to nivolumab dose level. Results to date suggest that the safety profile of nivolumab/ipilimumab combination therapy and nivolumab in combination with radiotherapy is consistent with the mechanisms of action of nivolumab and ipilimumab. The nature of the AEs is similar to that observed with either agent used as monotherapy; however, both frequency and severity of most AEs are increased with the combination.

A pattern of immune-related AEs has been defined, for which management algorithms have been developed; these are provided in nivolumab IB/SmPC or ipilimumab IB/SmPC. Most high-grade events were manageable with the use of corticosteroids or hormone replacement therapy (endocrinopathies) as instructed in these algorithms. For additional material, see the nivolumab IB/SmPC and ipilimumab IB/SmPC.

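### The safe/unsafe rule compares postoperative case counts with borders fixed for 50 recruited patients and never rescales them for treated patients whose postoperative course is not observed

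*Protocol*

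**What the plan says.** Section 6.1 defines the primary objective as safety, tolerability and feasibility of the regimen "following surgical resection, assessed by the latest" Clavien-Dindo classification and CTCAE. The synopsis represents safety and tolerability by three published outcomes in Table 1: any postoperative complication (39%), any surgical complication (23%) and reoperation (7%), from a series of 128.

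The verdict is a comparison of counts. Section 11.4.2 reads "Safety and tolerability will be assessed by comparing case numbers for any complication in the treatment arm (n=50" and refers to the upper limits in Table 2, which are computed for n=50. Under the synopsis decision rule, if the counts in both groups lie within their borders, H0 "is rejected and the treatment is considered as safe and tolerable". The treatment-arm border is recalculated in one situation only, a low count in the control arm. Table 3 gives reoperation stopping limits at 10, 20, 30, 40 and 50, and its footnote defines that index as "Number of recruited patients in the treatment arm".

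Section 7.1.6 requires withdrawal "in case of unacceptable toxicity". After a discontinuation on drug, "the investigations scheduled for the EOS visit will be performed 28 days after study drug discontinuation". Patients lost before the first cycle are replaced, but "All other drop-outs will be included in the sample size". Section 10.1 ends study-specific safety follow-up after the end-of-study visit. The visit schedule (Table 4) puts surgery in weeks 15 to 17 and the end-of-study visit in week 20.

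**The concern.** All three Table 1 outcomes can occur only after an operation. A treated patient who leaves before surgery, or is never operated on, cannot contribute a case to any of them, yet the limit stays at the value for 50. The more patients are lost in this way, the easier the limit is to meet.

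The loss is likely to be uneven. Section 9.2.1 says of the two drugs together that "both frequency and severity of most AEs are increased with the combination", and only the treatment arm receives them. Intolerance could therefore help the regimen to be labelled safe and tolerable, and could make the reoperation stopping rule slower to act.

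**Working it through.** **Checking the plan's own figures.** Section 11.2 says 49 treated patients can exclude a doubling from 23% to 46% with power 0.90 and α=0.05. A one-sided two-proportion comparison with the published 128 reproduces this. The pooled rate is (128×0.23 + 49×0.46)/177 = 0.294. Then z = [0.23 − 1.645×√(0.294×0.706×(1/128+1/49))] / √(0.23×0.77/128 + 0.46×0.54/49) = (0.23 − 0.126)/0.080 ≈ 1.30, which gives power 0.903. With 48 patients it is 0.899. All 15 rows of Table 2 and all 5 rows of Table 3 also reproduce: take the expected cases rounded half up, find the exact 95% limits for that count, multiply by n and round half up.

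**Timing.** Counting from the last dose, and taking surgery on days 105 to 119 (weeks 15 to 17) and the planned end-of-study visit on day 140 (week 20):

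| Last dose (day) | + 28 days (EOS investigations) | + 100 days (minimum AE collection) |
|---|---|---|
| 7 | 35 | 107 |
| 14 | 42 | 114 |
| 28 | 56 | 128 |
| 42 | 70 | 142 |

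The early end-of-study investigations always fall before surgery. The 100-day minimum runs past the surgery window after a last dose on day 28 or 42. After day 7 or 14 it ends inside that window.

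**Which border applies.** Table 2 has no 23% row. The 22.5% row gives 11 expected cases and an upper border of 18. Computed at 23%, 0.23×50 = 11.5 rounds to 12 cases, the exact upper limit is 0.3817, and 0.3817×50 = 19.1 gives a border of 19. Both are carried below.

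**Effect of unobserved patients.** Assume W of the 50 treated patients have no observed postoperative course and the other m = 50 − W have a true surgical complication rate of 46%. The probability of staying within border B is P(X ≤ B), with X binomial (m, 0.46). The protocol gives no value for W, so a range is shown.

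| W | m | B = 18 | B = 19 |
|---|---|---|---|
| 0 | 50 | 0.10 | 0.16 |
| 2 | 48 | 0.15 | 0.23 |
| 5 | 45 | 0.26 | 0.36 |
| 10 | 40 | 0.51 | 0.64 |

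**Border recalculated by the plan's method.**
- m = 45: 0.23×45 = 10.35, so 10 cases. Upper limit 0.3709×45 = 16.7, border 17. P(X ≤ 17) = 0.17.
- m = 40: 0.23×40 = 9.2, so 9 cases. Upper limit 0.3845×40 = 15.4, border 15. P(X ≤ 15) = 0.18.

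Starting from 22.5% gives the same two borders (10.125 rounds to 10, and 0.225×40 is 9), so the result does not depend on which row is used. If the true rate is 23%, the recalculated borders are met with probability 0.992 and 0.988, so a regimen at the published rate is rarely penalised.

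**Kept or excluded.** If the patient stays in the 50, the count has one fewer possible case and the border is 18 or 19. If the patient is excluded, under the treatment set in section 11.1 or the missing-data rule in section 11.4.1, the count again comes from m patients and is still compared with 18 or 19. The probability is the same.

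**The case against.** The strongest reply is that the protocol goes on observing most of these patients. Section 9.6 collects non-serious events for at least 100 days after the last dose. It requires SAEs over the same period, and later ones believed related to study drug or a protocol-specified procedure. Section 7.1.6 lets withdrawn patients ask that recording stop, which implies that it otherwise continues. Most of this stands: after a last dose on day 28 or 42 the collection period reaches past surgery, and 100 days is a minimum, not an end date. It leaves a gap mainly for last doses on day 7 or 14, and it cannot help for patients who are never operated on.

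A reader might infer that the protocol definitely keeps withdrawn patients in the 50 with no case. The documents do not settle that. The sentence on drop-outs is a replacement rule, while sections 11.1 and 11.4.1 point towards exclusion. The concern does not need it settled, because neither route changes the border.

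A reader might also infer that the trial is likely to declare an unsafe regimen safe. That is not supported. A probability of one half needs 10 of 50 (20%) wholly unobserved as well as a true doubling in the others, and no withdrawal rate is stated. Section 7.1.7 also allows termination for unacceptable adverse events or excessive drop-out. That is a matter of judgement and is not part of the verdict rule, but it makes the extreme cases less plausible.

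Finally, section 11.4.4 tabulates CTCAE events for everyone given at least one dose. Keeping toxicity descriptive is a legitimate choice in a trial without a formal sample size, so its absence from the binary verdict is not itself the fault raised here.

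**Conclusion.** The point holds in a limited form. The final rule and the reoperation stopping rule set raw postoperative counts against borders fixed for recruited patients, and nothing rescales those borders when fewer patients have an observed postoperative course. The direction is certain and favours a safe verdict. The size depends on an unknown number. With 2 unobserved patients the chance of missing a doubled surgical complication rate goes from 0.10 to 0.15 (border 18) or from 0.16 to 0.23 (border 19), which is modest. With 5 it is 0.26 or 0.36, and with 10 it is 0.51 or 0.64. Rescaling holds it at 0.17 to 0.18 for 5 and 10.

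These figures concern the surgical-complication border alone. They assume that the unobserved patients contribute no case at all and that the others share a common 46% rate. The change should be made because the rule issues a formal safety statement and the correction is small.

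**What to change.** 1. **Sections 7.1.6, 8.2.6 and 10.1.** State that patients who stop study drug or are withdrawn for toxicity remain in safety follow-up through surgery to the week-20 visit, unless they refuse further data recording.
2. **Sections 11.4.2 and 11.4.6, Tables 2 and 3.** Count complications among patients operated on with an observed postoperative course. Recalculate the lower and upper borders with binom.test, already named in section 11.4.7, for that number in each arm and at each interim look.
3. **Reporting.** Beside the verdict, give the number not operated on because of treatment-related toxicity or death before surgery. Do not count them as postoperative complications: the 39% reference describes events after surgery, and adding these patients would mix unlike events.

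The cost is a few extra visits, since surgery is standard care in any case, and slightly lower borders when some patients are not operated on. If everyone is operated on and observed, the borders stay at their n=50 values.

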| PATIENTS / GROUPS        | 
80 patients, 2 groups (50 treatment arm, 30 control arm)
 
Randomization ratio 30:50
                                                                                                                                                                                                                                                                                                                                                                                                                                                                                                                                                                                                                                                                                                                                                                                                                                                                                                                                                                                                                                                                                  |                   |                                           |                   |                                          |                   |

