**Table 1. Incidence of know complications for neoadjuvant CRT following surgical resection.**

| Complications (n=128)          | Percentage (%) | Citation |
|--------------------------------|----------------|----------|
| Any postoperative complication | 39             | [1]      |
| Any surgical complication      | 23             | [1]      |
| Reoperation                    | 7              | [1]      |

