### Sample size calculation

No formal sample size calculation was performed for this safety, tolerability and feasibility phase 2 study.

The 30:50 randomization ratio is a trade-off between having as much as possible patients in the treatment arm and enough patients in the control arm (standard of care treatment complication rates are well known).

The sample size of 80 is defined by the expected patient numbers available in the planned and financed duration time of the study (based on incidence, inclusion criteria and anticipated patient consent ratios). The primary objective (safety) can be compared to known and published values [1]. A doubling (100% increase) of any surgical complication (23% x 2 = 46%) can be excluded with 49 patients (Power=0.90;  $\alpha$ =0.05).

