| Stool biobanking               |          | X             |               |           | X         |           | X         |           |           |           |           |           | X          |           |
| Chest-Abdomen CT scan          |          | X             |               |           |           |           |           |           |           |           |           |           |            |           |
| Pelvis MRI                     |          | X             |               |           |           |           |           |           |           |           |           | X         |            |           |
| Surgery                        |          |               |               |           |           |           |           |           |           |           |           |           | X          |           |
| Adverse Events                 |          |               | X             | X         | X         | X         | X         | X         | X         | X         | X         | X         | X          | X         |
| EORTC QLQ                      |          |               |               |           | X         |           | X         |           | X         |           |           | X         |            |           |

\*only for treatment arm (SOC+IMP)

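### No direct randomised comparison enters the primary safety decision, so the rule can declare the treatment safe when the randomised arms show a clear excess of complications

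*Protocol*

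**What the plan says.** The hypotheses in the synopsis (Section 2) are comparative: H1 states that adding ipilimumab and nivolumab to chemoradiotherapy does not raise surgical complication rates. The trial randomises 50 patients to treatment and 30 to control.

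The primary analysis in Section 11.4.2 compares treatment-arm case numbers "with the calculated 95% upper CI numbers of the calculated percentage of expected numbers of current standard therapy". The controls have a different task: "Case numbers in the control arm (n=30) will be used to validate expected numbers from current standard therapy".

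The decision rule stands in the synopsis, in the paragraph below Table 2:

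- If each arm's count lies within its own borders, H0 is rejected and the treatment is called safe.
- If the treatment count is above its upper border, the treatment is called unsafe for that complication.
- One branch lets the controls change the limit. It begins "If case numbers for a specific complication are below the corresponding" lower border in the control group; new treatment-arm limits are then calculated from the observed control count.
- A control count above its upper border has no stated consequence.

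Between-arm tests appear in Section 11.4.3, for secondary objectives. Section 11.4.4 tabulates adverse events by arm, descriptively. The synopsis justifies the smaller control arm by saying that standard-of-care complication rates are well known.

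**The concern.** The concurrent controls share the treatment arm's surgeons, case mix and period. They are the reference that randomisation provides for the comparative H1. The primary decision uses them mainly to check whether a published rate is plausible, and the borders for that check are wide: 3 to 13 of 30 for surgical complications and 0 to 7 of 30 for reoperation. A control arm doing much better than the published series can pass the check while the treatment arm does much worse and still stays under its own limit. The protocol would then conclude that the treatment does not increase complications when its own randomised data point the other way. In the opposite direction, a locally high complication rate common to both arms can be read as drug toxicity.

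**Working it through.** **The plan's own figures.** The synopsis states: "A doubling (100% increase) of any surgical complication (23% x 2 = 46%) can be excluded with 49 patients", with power 0.90 and α 0.05; sidedness is not given. Comparing n treated patients with the 128 patients of Table 1 (one-sided, pooled normal approximation) at n = 49:

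- pooled rate = (128×0.23 + 49×0.46)/177 = 0.294
- SE under H0 = √[0.294×0.706×(1/128 + 1/49)] = 0.0765
- SE under H1 = √[0.23×0.77/128 + 0.46×0.54/49] = 0.0803
- power = Φ[(0.23 − 1.645×0.0765)/0.0803] = 0.903; n = 48 gives 0.899

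So 49 is reproduced. That it was obtained this way is an inference.

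**Borders.** Table 2 follows from exact (Clopper-Pearson) limits multiplied by n and rounded half up; all 15 rows match. It has no rows at 7%, 23% or 39%, so the nearest rows are used. For 7% and 39%, computing at the exact rate gives the same borders. For 23%, the expected treatment count becomes 12 instead of 11 and the upper border 19 instead of 18.

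| Complication (row used) | Control borders, of 30 | Treatment upper border, of 50 |
|---|---|---|
| Reoperation (7.5%; also Table 3) | 0 to 7 | 10 |
| Any surgical (22.5%) | 3 to 13 | 18 |
| Any postoperative (40%) | 7 to 18 | 27 |

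**Outcomes inside both borders.** Fisher's exact test is two-sided. The interval is Newcombe's: d − √[(p₁−l₁)² + (u₀−p₀)²] to d + √[(u₁−p₁)² + (p₀−l₀)²], with Wilson limits l and u for each arm. For 18/50 against 3/30 the Wilson limits are 0.241 to 0.499 and 0.035 to 0.256, and d = 0.36 − 0.10 = 0.26. The lower limit is 0.26 − √(0.119² + 0.156²) = 0.064; the upper limit is 0.26 + √(0.139² + 0.065²) = 0.413.

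| Complication | Treatment | Control | Difference, points (95% CI) | p |
|---|---|---|---|---|
| Reoperation | 10/50 | 0/30 | 20 (6 to 33) | 0.011 |
| Any surgical | 18/50 | 3/30 | 26 (6 to 41) | 0.017 |
| Any postoperative | 27/50 | 7/30 | 31 (8 to 48) | 0.010 |

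With the border at 19, 19/50 against 3/30 also passes (p = 0.009).

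**The reset branch.** For surgical complications, control counts of 0, 1 or 2 of 30 give new treatment upper borders of 4, 7 and 8 of 50. A significant excess would need 7, 10 and 13, so none can pass. The protection stops abruptly: at 3 of 30 the limit returns from 8 to 18. For reoperation a count below 0 is impossible, so the limit stays at 10 even with no control events.

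**How often.** Probability that one complication is inside both borders and also shows a significant excess, for assumed true rates (control, treatment):

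| Complication | Rates | Probability |
|---|---|---|
| Any surgical | 23%, 23% | 0.5% |
| Any surgical | 23%, 46% | 0.7% |
| Any surgical | 23%, 36% | 2.4% |
| Any surgical | 10%, 36% | 10% |
| Any postoperative | 39%, 54% | 3.6% |
| Any postoperative | 26%, 52% | 12% |
| Reoperation | 7%, 14% | 7.3% |
| Reoperation | 7%, 20% | 9.0% |

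The reoperation figures ignore the interim looks of Table 3, which would lower them. With the border at 19, the 10% against 36% scenario rises to 16%.

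**High rate in both arms.** If the true surgical rate were 40% in both arms (an assumption), P(more than 18 of 50) = 66%: the treatment would be labelled unsafe with no treatment effect.

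**Precision of the randomised contrast.** Half-width at 23%: 1.96×√[0.23×0.77×(1/50 + 1/30)] = 19.0 points. For 23% against 46% with 30 and 50 patients the pooled rate is 29.9/80 = 0.374, and two-sided power is Φ[(0.23 − 1.96×0.1117)/0.1043] = 54% (50% with Fisher's test).

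**The case against.** The historical reference is a declared choice in a safety and feasibility phase II trial with no formal sample size calculation. The border rule is also the more sensitive detector of a large absolute rate: at a true 46%, more than 18 of 50 occurs with probability about 90%, against about 50% for significance in a between-arm Fisher test. Ninety per cent two-sided power between arms at 30:50 would need 71 controls and 119 treated patients. All of this stands. It is a reason to keep the border rule, but it does not explain why a comparative H1 should be accepted without looking at the randomised difference.

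Three stronger readings are tempting, and the protocol does not support them:

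- A reader might infer that the controls never affect the verdict. They do when their count is below the lower border, and no significant excess passes in that branch.
- A reader might infer that the rule commonly clears a harmful treatment against the randomised evidence. The conflict needs a control count that is low but still inside its borders: 3 or 4 of 30 for surgical complications (5 if the border is 19), 7 to 9 for postoperative and 0 or 1 for reoperation. At the doubling named in the protocol, 23% to 46%, it occurs in under 1% of trials.
- A reader might see a bias in the surgical counts because the week 9 and week 12 visits are for the treatment arm only (Table 4). Those visits precede surgery in weeks 15 to 17. They concern adverse-event and laboratory ascertainment, not the postoperative complications of Table 1.

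**Conclusion.** The point holds in this form: the primary safety decision contains no direct randomised comparison, and the single branch in which the controls set the limit covers only counts below the lower border, which is unreachable for reoperation. The rule can therefore return a safe verdict with a randomised 95% CI wholly above 0 for each of the three Table 1 complications. The frequency is small, roughly 1 to 10% in most scenarios computed (extremes 0.5% and 12%, or 16% with the border at 19), but what is affected is the trial's primary conclusion. Separately, a control count above its upper border leads to no re-basing, so a shared high rate is attributed to the treatment.

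Assumptions: nearest printed rows of Table 2; independent binomial counts with all 50 and 30 patients evaluable; and a count equal to a border taken as inside it, because the synopsis attaches consequences only to counts above or below. If border values were excluded, the three outcomes tabulated would drop out, though 26/50 against 8/30 postoperative complications would still pass with a significant excess.

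**What to change.** Keep the historical border rule and the re-basing below the lower border. In Section 11.4.2 and in the decision paragraph below Table 2, add:

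1. For each Table 1 complication, report the between-arm risk difference with a 95% CI (Newcombe or Miettinen-Nurminen).
2. Do not conclude that the treatment is safe for a complication when that interval lies wholly above 0, even if both counts are inside their borders.
3. When the control count exceeds its upper border, interpret the treatment count through the between-arm difference and not through the historical border alone. Since a shared high rate can leave the controls just inside their border, show the difference beside every border verdict.
4. State which upper border applies to the published 23%: 18 (the 22.5% row) or 19 (computed at 23%).

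The complication counts are already collected in both arms, so the cost is analysis wording; the reoperation cutoffs of Table 3 are not touched. The limitation to state in the text is precision: about ±19 points at 23%, and only about 50 to 54% two-sided power for 23% against 46%. An interval that includes 0 is therefore not evidence of safety, and the added contrast is a check on the border rule, not a substitute for it.
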